#### Urine samples

Urine samples are collected at home by the participant on the morning that they attend the study visit. The sample should be taken from first midstream urine in the morning after overnight fasting. At the hospital 5 ml are frozen at −80 °C in sterile tubes (Falcon 15-ml polypropylene) containing 50 μl NaN_3_.

#### Vaginal samples

Vaginal samples are collected at home using an eSwab and sent by mail. eSwab is a liquid-based multipurpose collection and transport system that maintains the viability of aerobic, anaerobic and fastidious bacteria for up to 48 h.

#### Blood samples

Blood samples will be taken at every study visit during the study period. They will be analyzed for concentrations of i.a. lipids and lipoproteins (high-density lipoprotein (HDL), low-density lipoprotein (LDL) and total cholesterol), inflammatory markers (CRP, interleukin (IL)-18, IL-6 and tumor necrosis factor alpha (TNF-α)), Glycated hemoglobin (HbA1c) level, homocysteine, GLP-1 and BDNF (brain-derived neurotrophic factor). At study visits during pregnancy the participants will be fasting.

#### Breast milk samples

Breast milk samples will be collected at all study visits after birth. Samples are taken on the day of the study visit. The samples are frozen at −80 °C at the hospital.

### Hospital chart review

Hospital records directly related to pregnancy and delivery will be reviewed. Pregnancy complications and mode of delivery will be extracted from hospital files and validated using the Danish national guidelines. GDM will be defined according to the International Association of Diabetes in Pregnancy Study Group (IADPSG) criteria, to be able to compare results from this study with other international studies. Preeclampsia will be defined as proteinuria (dipstick, greater than 1+ protein) and persistently elevated blood pressure greater than 140/90 mmHg on more than one occasion. Gestational hypertension is diagnosed using the same criteria but without proteinuria. Macrosomia is defined as birthweight of 4000 g or greater. The z-score of the newborn will be calculated (deviation from the expected weight corrected for gestational age and sex) [33]. Apgar scores and eventual delivery complications will also be registered. All admissions to the neonatal care unit will also be recorded along with diagnosis for admission. Women who choose to withdraw from the study will be asked if they will allow review of their hospital records for the purpose of comparing “drop-outs” with women who remain in the study.

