
### Aims and hypotheses

In a pilot study of 50 obese pregnant women, we aim to investigate if the probiotic Vivomixx® can affect gestational weight gain, glycated hemoglobin (HbA1c) level and reduce impairment of glucose tolerance at gestational weeks 27–30, compared to weeks 14–20, in obese pregnant women. The aim of conducting an initial pilot study (*n* = 50) is to clarify feasibility and compliance and to estimate parameters, such as the standard deviation, which will be used in a sample size calculation for a full-scale trial. The study will also give an estimate of the proportion of eligible women who are willing to participate, of participants who drop out of the trial and of participants who comply with their allocated intervention.

Secondary aims are:To examine changes in microbiota and inflammatory markers in mother and child (in fecal samples)To examine changes in vaginal microbiological profile and frequency of urinary tract infections (including group B streptococcus infections)To examine changes in concentrations of lipids and inflammatory markers (maternal blood sample)To assess if the intervention reduces the risk of complications during pregnancy and at birth – including GDM, preeclampsia, gestational hypertension, change in the mode of delivery, gestational age, macrosomia (birth weight of over 4000 g) and large- and small-for-gestational-age infantsTo examine the impact of the intervention on diet, physical activity levels and breastfeedingTo examine differences in the neonatal outcome – weight, z-score, Apgar score after 5 min, umbilical cord pH, and the risk of early neonatal transfer to the neonatal intensive care unitTo assess the child’s weight gain and body composition until 9 months of age (dual-energy X-ray absorptiometry (DEXA) scanning (at birth) and skin-fold measurements thereafter)

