### Assessment of primary outcomes

Gestational weight gain is the primary outcome. Maternal weight gain is defined as weight at gestational age 36–37 weeks minus self-reported prepregnancy weight. All women are weighed at the same scale at every study visit, wearing light clothing and no shoes (Seca digital scales, Seca, Hamburg, Germany). GWG values are calculated as the difference between the mother’s prepregnancy weight and her weight at 36–37 weeks of gestation.

The other primary outcome is the change in maternal fasting glucose from weeks 14–20 (preintervention) to weeks 27–30 between probiotic and placebo groups. GDM outcomes are assessed at 14–20 and 27–30 weeks’ gestation by a three-time-point 75-g OGTT. Preparation for the test includes a 10–13-h pretest fast with instructions to avoid smoking and chewing gum during this time and during the test. Tap water intake should be limited to two glasses (300 ml) and exercise on the morning of the test should be avoided. Participants remain in a resting state during the test.

Measurements are listed in Table 1.

**Table 1 Tab1:** Maternal and neonatal/infant primary and secondary outcomes

Measurement	Inclusion/randomization (14–20 weeks)	27–30 weeks	36–37 weeks	Delivery	1–3 days after delivery	3 months after delivery	6 months after delivery	9 months after delivery
Baseline questionnaire	X							
Diet questionnaire	X		X					
Weight (pregnant/mother)	X	X	X		X	X	X	X
Blood sample (pregnant/mother)	X	X	X		X	X		X
Blood pressure	X	X	X					
Fecal sample (pregnant/mother)	X	X	X		X	X	X	X
Urine sample + vaginal swab	X	X	X					
Pedometer	X	X	X					
OGTT	X	X						
Fecal sample – infant					X	X	X	X
Urine sample – infant					X	X	X	X
Newborn – umbilical cord blood sample				X				
DEXA scanning					X			
Breast milk sample					X	X	X	X
Newborn/child physical examination and anthropometric data					X	X	X	X
Question about urinary tract infections	X	X	X					
Question about colic symptoms, breastfeeding, allergy and atopic dermatitis						X	X	X

*DEXA* dual-energy X-ray absorptiometry, *OGTT* oral glucose tolerance test

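### Women who withdraw or deliver before the 36–37-week visit have no GWG as defined, and the one stated use of withdrawn women's records does not bring them into the comparison by arm

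*Protocol article*

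**What the plan says.** Under Assessment of primary outcomes, the first primary outcome is fixed by one end weight: "Maternal weight gain is defined as weight at gestational age 36–37 weeks minus self-reported prepregnancy weight". The weight comes from study visits: "All women are weighed at the same scale at every study visit". No substitute is given for a woman who has no such visit. Table 1 schedules maternal weight at inclusion (14–20 weeks), at 27–30 weeks and at 36–37 weeks.

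The second primary outcome in that section ends earlier: "The other primary outcome is the change in maternal fasting glucose from weeks 14–20 (preintervention) to weeks 27–30".

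Under Hospital chart review, the general rule is "Hospital records directly related to pregnancy and delivery will be reviewed". Women who withdraw are handled in a separate sentence, which begins "Women who choose to withdraw from the study will be asked if they will allow review of their hospital records for the purpose of comparing"; the purpose in full is "for the purpose of comparing “drop-outs” with women who remain in the study". No further use of their records is named.

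Under Aims and hypotheses, the pilot is to estimate the proportion "of participants who drop out of the trial and of participants who comply with their allocated intervention". Loss is therefore foreseen, but no rate is assumed. Sample size and statistics bases its power on 25 women per arm with no allowance for loss, and names simple two-group tests by treatment. (The test types given there for continuous and categorical data appear to be interchanged, which is a separate matter.)

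**The concern.** Treatment starts at 14–20 weeks and the GWG weight is taken at 36–37 weeks, so 16 to 23 weeks pass in which a randomised woman can be lost to this outcome (36 − 20 = 16; 37 − 14 = 23). The loss need not be unrelated to treatment. Gestational age at birth and preeclampsia are among the outcomes that the intervention is meant to influence, and an early delivery removes the woman from the GWG comparison. Withdrawal may likewise follow complications, tolerance or weight itself.

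For secondary outcomes the remedy is close at hand. GDM, preeclampsia, gestational hypertension, mode of delivery, birth weight and neonatal admission can be read from the chart whether or not the woman still attends. The aims ask whether the intervention reduces these risks, which calls for the groups as randomised. The stated reason for opening withdrawn women's charts is a different comparison, between those who left and those who stayed.

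At stake are the balance that randomisation provides, some precision in a small sample, and the standard deviation that the pilot is to hand on to the full-scale trial.

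**Working it through.** **1. The plan's own power.** Inputs from Sample size and statistics: n = 25 per arm, difference 2 kg (10 against 8), SD 6.5, α = 0.05 (taken as two-sided).

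- SE = 6.5 × √(2/25) = 1.838 kg
- Normal approximation: Φ(2/1.838 − 1.96) = Φ(−0.872) = 0.192
- Noncentral t with 48 df: 0.187

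Both round to the stated 19 %. A one-sided test would give 0.289, so two-sided is the right reading. The figure holds only if all 50 women supply a GWG value.

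**2. Width of the confidence interval.** For the difference between arms, 2 × t(0.975; 48) × SE = 2 × 2.011 × 1.838 = 7.4 kg. The article states an expected width of 5. That matches the mean of a single arm (2 × 1.96 × 6.5/√25 = 5.1 kg), not the difference, so 7.4 kg is the reference below.

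**3. Loss of the 36–37-week weight.** The article gives no rate, so the loss is an assumption. Same formulas, t-based:

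| Women with GWG per arm | Lost of 50 | SE (kg) | CI width (kg) | Power |
|---|---|---|---|---|
| 25 | 0 | 1.838 | 7.4 | 18.7 % |
| 22 | 6 (12 %) | 1.960 | 7.9 | 16.9 % |
| 20 | 10 (20 %) | 2.055 | 8.3 | 15.8 % |

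The normal approximation agrees closely: at 10 to 30 % loss the width is 7.6 to 8.6 kg and power 17.7 to 14.7 %.

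**4. Bias in a comparison of women with a GWG value.** Let d be the proportion lost in an arm and g the mean GWG of those lost minus that of those retained. The retained mean then differs from the full-arm mean by −d × g, and the difference between arms shifts by −(d_T × g_T − d_C × g_C). All values of d and g below are assumed.

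| d_T | d_C | g, same in both arms (kg) | Shift (kg) |
|---|---|---|---|
| 20 % | 20 % | 3 | 0 |
| 20 % | 10 % | 3 | −0.3 |
| 30 % | 10 % | 3 | −0.6 |
| 30 % | 10 % | 5 | −1.0 |

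Equal loss with an equal gap gives no shift. The last row is half of the planned 2 kg effect. Equal loss is not enough if the gap differs: with 20 % lost in each arm, g = 3 kg in one and 0 in the other, the shift is 0.2 × 3 = 0.6 kg.

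**5. Charted outcomes.** One woman is 1/25 = 4 percentage points of an arm, so one or two events in withdrawn women would move a rate by up to 4 or 8 points, if those events were left out.

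**6. Which outcomes are affected.** GWG needs the 36–37-week visit. Fasting glucose change needs only the 27–30-week visit, so a woman lost after that visit is missing from GWG but not from glucose.

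**The case against.** The case against is substantial, and most of it limits the point rather than removing it.

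- A reader might infer that withdrawn women's records serve the drop-out comparison and nothing else. The text names one purpose; it does not exclude others.
- A reader might infer that the arms will be compared among completers. The article nowhere says so. It names no exclusion and no per-protocol set. The analysis set and the handling of missing weights are commonly left to an SAP or full protocol, and neither is shown.
- A reader might infer that women who stop their capsules are no longer followed. Nothing supports this. The aims count drop-out and compliance separately, the compliance section sets an 80 % expectation without attaching removal to it, and all women are to be weighed at every study visit.
- Asking permission in order to describe attrition is sound practice and fits a pilot that aims to estimate drop-out.
- The weight at 27–30 weeks is already scheduled, and nothing forbids its use.
- The loss rates are assumed, and the effect on precision is small in a study with 19 % power at best.

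All of this stands. It does not answer two things that the article itself fixes. GWG has a single end weight with no alternative. The purpose put to a withdrawing woman is worded narrowly, and an SAP written later may not be able to widen a permission already given.

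**Conclusion.** The point holds in a limited form. Followed as written, the GWG definition leaves women who withdraw or deliver before the 36–37-week visit without this primary outcome. The one stated use of withdrawn women's records gives their charted outcomes no place in the comparison by arm. The documents do not show that the analysis will rest on a selected subset; they name no route that avoids it.

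The cost in precision is modest: CI width 7.4 to 7.9–8.3 kg and power 19 % to about 17–16 %, if 12 to 20 % of women lack the last weight (SD 6.5, difference 2 kg, two-sided 5 %, equal loss). Bias lies between none and about 1 kg in the scenarios tried, and arises only if loss, or its relation to weight, differs between arms. The article gives no figure for either. The change is worth making because it is cheap and because the permission wording is hard to repair afterwards.

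**What to change.** 1. **Hospital chart review.** Reword the sentence on withdrawing women so that the permission covers use of their charted pregnancy and birth outcomes in the comparison by allocated group, as well as the comparison of drop-outs with those who remain.
2. **Weight analysis.** Replace the two-group test on a single end weight by a repeated-measures model of the measured weights at 27–30 and 36–37 weeks, adjusted for measured weight at randomisation, with all randomised women in their allocated group. The treatment effect at 36–37 weeks is the main result. GWG from self-reported prepregnancy weight can still be reported beside it.

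**Cost.** Revised wording, with whatever approval a change in the permission requires, and a little more analysis. No new visits or measurements are needed: chart review and both weights are already planned. Trial status gives 20 women included by November 2015, so revised wording could serve the other 30 of the planned 50, and any of the 20 who withdraw later.

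**Limits.** Some withdrawing women may refuse the permission. The model assumes that missing weights are explained by the observed ones. Women lost before 27–30 weeks still add little to the weight comparison.

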### DEXA scanning and infant examination

A DEXA scan is conducted before 72 h post birth for the newborn and the parents. The method is validated in the newborn [34]. The infants will be weighed recumbent (Seca 727, digital baby scales, Seca, Hamburg, Germany), and their length and head circumference are measured with a measuring tape according to World Health Organization guidelines. Abdominal circumference is measured at the umbilical level in the supine position during mid-expiration. Newborn anthropometric measurements are collected from their birth chart.

### Subject compliance monitoring and capsule viability

Patient compliance will be monitored by requesting the patients to return all unused capsules at the visit at gestational weeks 27–30 and at follow-up after delivery. The patient should consume at least 80 % of the study medication during the study period. Fecal samples are collected from participants and it will be proven whether the probiotic bacteria are established in the gut of the intervention group by using strain-specific primers. Samples of capsules returned from the participants will be tested to ensure that the capsules have maintained their viability.

### Safety and adverse event monitoring

Probiotic bacteria are widely occurring intestinal bacteria and interventional studies with probiotic bacteria are generally considered to be safe. Probiotic bacteria are used in fermented dairy products and other foods including some infant formulas. Moreover, there is a wide range of commercial products available at pharmacies and health food stores.

All strains included in Vivomixx® are known and accepted organisms in food and have been used in clinical studies in the form of VSL#3 in obese children with nonalcoholic steatohepatitis [27], patients with inflammatory bowel disease [35–37], critically ill patients [38], patients with cirrhosis [39, 40] and pediatric patients [41, 42] with no reported side effects.

Clinical studies on pregnant women and infants also support the safe use of probiotics during pregnancy and early infancy [22, 43, 44].

Participants are asked about side effects of the product at every study visit and their answers are recorded in the CRF.

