The etiology of the development of obesity is not clearly elucidated, but a complex interaction between genetic, epigenetic and social factors is likely. The prevalence of obesity has been rising faster than can be explained by biological variation, indicating that genetics is not the only cause [19]. In addition, there is small but consistent evidence showing that the daily consumption of probiotics may reduce the risk of preeclampsia [20], maintain serum insulin levels [21] and reduce the frequency of GDM [22] in pregnant women. Vivomixx® consists of eight strains of freeze-dried probiotic bacteria. The product contains the same mixture of bacteria as the product VSL#3 and some studies demonstrate that VSL#3 may normalize gut permeability and barrier function, which is associated with beneficial anti-inflammatory and immunomodulatory properties [23, 24]. A new study on mice has demonstrated that the administration of VSL#3 can prevent and treat obesity and diabetes in several mouse models and suppress body weight gain and insulin resistance via modulation of the gut microbiota [25]. VSL#3 promotes release of the hormone glucagon-like peptide 1 (GLP-1) resulting in reduced food intake and improved glucose tolerance. The VSL#3-induced changes are associated with an increase in the levels of a short chain fatty acid (SCFA), butyrate [24]. Butyrate stimulates the release of GLP-1 from intestinal L-cells thereby providing a plausible mechanism for VSL#3’s action. Promising results have also been shown in humans. A randomized controlled study by Rajkumar et al. in 2014 among 60 overweight (BMI >25) but otherwise healthy adults showed a significant reduction in total cholesterol, triglycerides, low density lipoproteins (LDL) and very-low-density lipoproteins (VLDL) (*P* < 0.05) after 6 weeks of VSL#3 treatment. They also found improved insulin sensitivity (*P* < 0.01), decreased C-reactive protein (CRP), and a favorable effect on the composition of gut microbiota [26]. A randomized study by Alisi et al. in 2014 examined the beneficial effects of VSL#3 in 48 obese children with nonalcoholic steatohepatitis. After 4 months of treatment, BMI was significantly reduced and GLP-1 secretion increased in the VSL#3-supplemented children compared to the placebo group (*P* < 0.001) [27]. Moreover, VSL#3 has also been tested in a small interventional study among 27 healthy pregnant women by Vitali et al. in 2012 in order to investigate changes in the composition of the vaginal microbiota and cytokine secretion. VSL#3 was administered during the last trimester of pregnancy and was associated with modulation of the vaginal microbiota and cytokine secretion [28]. None of the studies [25–27] reported side effects related to the treatment with VSL#3. As accumulating evidence indicates that the gut microbiota plays a significant role in obesity and because the “ideal” composition of the gut microbiota remains poorly understood, modulation of the gut microbiota composition represents a potentially attractive treatment option against excessive GWG and adverse outcomes for mothers and infant. Dietary supplements in the form of probiotics could potentially be beneficial for controlling weight gain in pregnancy by inducing changes in the gut microbiota and could also affect the infant’s microbiota, which may have important implications for infant development and health.

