### Data handling and record keeping

Case Report Forms (CRF) will be used to record data for all participants, and data will be double-entered on an electronic database to secure its validity. Questions in the CRF collect a range of data including effect modifiers (antibiotics), outcome data and adverse events. The research staff is the same two people throughout the study to standardize the data collection procedure.

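### The safety question asks blinded women for side effects they blame on the capsule, which is narrower than the adverse events the CRF is said to collect and leaves three kinds of event with no stated route

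*Protocol article*

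**What the plan says.** Under *Safety and adverse event monitoring*, the only instruction on asking about harms is "Participants are asked about side effects of the product at every study visit and their answers are recorded in the CRF". Under *Data handling and record keeping*, the content of the CRF is described more widely: "Questions in the CRF collect a range of data including effect modifiers (antibiotics), outcome data and adverse events".

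Other sections supply further routes:

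- *Hospital chart review*: "Hospital records directly related to pregnancy and delivery will be reviewed". From these files, "Pregnancy complications and mode of delivery will be extracted from hospital files and validated using the Danish national guidelines" and "Apgar scores and eventual delivery complications will also be registered". Every neonatal-unit admission is noted with its diagnosis.
- *Hospital chart review*, on drop-outs: "Women who choose to withdraw from the study will be asked if they will allow review of their hospital records". The stated purpose is to compare them with the women who stay.
- *Assessment of primary outcomes*, Table 1: a urinary tract infection question at the three pregnancy visits; an infant physical examination at 1–3 days and at 3, 6 and 9 months; and, at 3, 6 and 9 months, "Question about colic symptoms, breastfeeding, allergy and atopic dermatitis".

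**The concern.** An adverse event is normally recorded whatever its cause, and relatedness is judged afterwards. The safety section reverses that order: the participant does the causal filtering before anything is written down, and does so without knowing her allocation. Staff who follow that sentence would not produce the unconditional adverse event data that the data-handling section describes.

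The setting makes this matter. The women take capsules from weeks 14–20 to delivery, and the infants are followed to 9 months because the intervention is expected to act on their microbiota. An infant takes no capsule, so a question about product side effects fits infant illness poorly. The pilot is also meant to estimate drop-out and compliance for a full-scale trial, and a side effect that makes a woman leave bears on both.

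**Working it through.** The plan gives no figure on this point, so the check sets each stated route against the kinds of event it could pick up.

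| Route | Depends on the woman's view of cause? | Covers |
|---|---|---|
| Safety question | Yes, and on attendance | Whatever she blames on the capsule |
| CRF items | Not stated | Adverse events (no wording given), antibiotics |
| Chart review | No | Pregnancy complications, mode of delivery, delivery complications, Apgar scores, neonatal-unit admissions |
| Table 1, mother | No | Urinary tract infections |
| Table 1, infant | No | Findings on examination; colic, allergy, atopic dermatitis |
| Record review of withdrawers | No, but needs permission | Hospital records |

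**Mother.** Obstetric events come from the chart, urinary tract infections from Table 1 and antibiotic courses from the CRF. What remains is illness or hospital contact unrelated to pregnancy that she does not link to the capsule. Chart review is confined to pregnancy and delivery records, so it does not reach these events.

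**Infant.** Delivery and neonatal-unit events are covered. At 3, 6 and 9 months the examination shows what is present that day, and the symptom questions name three conditions besides breastfeeding. An infection or admission between visits that has resolved and falls outside those items is not sought.

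**Stopping or withdrawal.** A woman who stops because of a side effect has already blamed the capsule, so here attendance is the obstacle. If capsules start at the baseline visit, the next visit comes between 27 − 20 = 7 and 30 − 14 = 16 weeks later. A woman who leaves before then has no scheduled visit at which the question is put. The contact about her records is described for another purpose, and a symptom managed at home need not appear in a hospital file.

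**Effect on a comparison of arms.** Let the true event risks be p1 and p0, and suppose the same share a of events is attributed in both arms, as blinding would favour. The recorded risks are a·p1 and a·p0. The recorded difference is a(p1 − p0), smaller than the true one whenever a < 1; the ratio stays p1/p0. Counts and absolute differences shrink, while the expected ratio does not change. The article gives no value for a, p1 or p0, so no number of missed events can be derived.

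**The case against.** The strongest reply is that a condensed article's summary sentence should not be read as the whole collection procedure. The CRF is said to hold adverse events without condition, and event definitions, form wording and seriousness fields commonly sit in the full protocol. That stands as far as it goes: their absence here is no finding. It does not remove the mismatch, because the article does state an elicitation rule, and that rule is narrower than its own section heading and than the CRF description.

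A reader might infer that safety rests on this question alone, or that most infant events are lost. The documents do not support either. Chart review, the antibiotic item, the urinary tract infection question, the repeated infant examinations and the infant symptom questions all work without attribution. Nor is it right that no contact takes place at withdrawal, since withdrawers are asked about access to their records. The article is silent on whether their reasons or symptoms are noted then.

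A reader might also conclude that the plan rests light monitoring on a misuse of earlier safety data. The article does not say that monitoring was lightened for that reason, and its Background sentence, "None of the studies [25–27] reported side effects related to the treatment with VSL#3", is already restricted to the studies it names. Finally, safety is not among the pilot's stated aims, and the aim on drop-out is to estimate its proportion, not to explain it.

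**Conclusion.** The point holds in a limited form. The stated safety question filters events by perceived cause and by attendance, and does not match the CRF content described elsewhere. If it is applied as written, three groups of event have no stated route: non-obstetric maternal illness not blamed on the capsule, post-neonatal infant illness or admission outside the listed items, and side effects behind stopping or withdrawal.

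The size can be given only as these categories. Any percentage missed would need an event rate and an attribution share that the article does not supply. The conclusion assumes that staff ask the question as the safety section words it; if the CRF already carries a cause-neutral question, the remedy is to say so. This is a worthwhile improvement to a stated method. It does not affect the randomisation or the primary outcomes.

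**What to change.** Reconcile *Safety and adverse event monitoring* with *Data handling and record keeping* by replacing the side-effect sentence with wording such as:

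> At each study visit, and at the contact when a woman withdraws, the same open question is asked about any new symptom, illness or hospital contact in the mother and, after birth, the infant, whatever the suspected cause. Relatedness to the capsules is recorded separately under blinding. All events, and the subset judged related, are tabulated by arm.

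Add infant infections and admissions to the existing 3-, 6- and 9-month infant questions in Table 1.

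No new visits are needed. The costs are revised CRF wording, a few minutes per visit, a short enquiry at withdrawal, and more unrelated minor events to record and tabulate. Because 20 of the planned 50 women had been included by November 2015, the date of any change should be recorded so that answers to the two wordings can be told apart.
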